**Study Population**

We will identify all male patients over the age of 18 with an incident exposure to a PDE5 inhibitor from 1^st^ July 1999 to 1^st^ August 2014 inclusive. The reasoning behind the proposed study period is that the restrictions regarding the prior diagnoses required to receive a PDE5 inhibitor prescription were imposed on 1^st^ July 1999, and restrictions for generic sildenafil were lifted on 1^st^ August 2014, after Pfizer’s sildenafil patent expired on 21^st^ June 2013. Follow up will begin at the date of first PDE5 inhibitor prescription (hereafter the “index date”). Exposed patients will matched to up to four controls on age at first prescription (within 3 years in either direction), GP practice, diabetes status, and their index date will be the same as their matched case’s. All matching variables will be measured at the index date. Patients with any cancer diagnoses prior to the index date will be excluded. Individuals selected as controls may later go on to start a PDE5 inhibitor; in this situation they will be censored as a control at the time of starting a PDE5 inhibitor, and they will contribute separately as an exposed patient from that time point (with their own matched controls).

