**Statistical/analysis plan**

Within the cohort, a patient’s observation time will begin at the index date and will end when one of the following occur: incident malignant melanoma, at diagnosis of a cancer other than malignant melanoma, death, transfer out of CPRD network, prescription of a PDE5 inhibitor (for unexposed controls), or end of follow up. The following analyses will be carried out using incident malignant melanoma as the primary outcome.

*Descriptive analyses*

Prior to exploring the relationship between PDE5 inhibitors and malignant melanoma, we will firstly describe the distribution of exposed and unexposed within the following variables: age, ever prescribed a PDE5 inhibitor, GP practice region (North East, North West, Yorkshire & the Humber, East Midlands, West Midlands, East of England, South West, South Central, London, South East Coast, Northern Ireland, Scotland, Wales), diabetes status, smoking status (non-smoker, current smoker, ex-smoker), BMI (underweight, normal, overweight/obese), alcohol status (non-drinker, current drinker, ex-drinker), index of multiple deprivation score.

*Ever exposed vs. never exposed to a PDE5 inhibitor*

Crude incidence ratios will firstly be calculated. The main exposure variable will then be included in an unadjusted and adjusted Cox regression model (see “Confounding” below), stratified by matched set to account for the matching. The primary outcome will be a diagnosis of incident melanoma and patients will be censored at diagnosis of any other cancer, death, transfer out of the CPRD network, or on 21^st^ June 2013 (end of follow up). Hazard ratios and 95% confidence intervals will be estimated, comparing the rate of incident melanoma between patients who have ever been prescribed a PDE5 inhibitor and patients that have never been prescribed a PDE5 inhibitor. We will also calculate changes in absolute risk of melanoma by obtaining predictions from a Poisson model with the same covariates as our main Cox model, plus time since index date (time-updated).

*Cumulative duration of exposure*

Unadjusted and adjusted Cox regression models will then be re-run using a time updated variable capturing the cumulative number of PDE5 inhibitor prescriptions in place of the ever exposed variable. Hazard ratios and 95% confidence intervals will again be estimated.

*Confounding*

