Age, GP practice, diabetes status and calendar time are matching variables. Our models will also be adjusted for the following potential confounders evaluated at beginning of follow up:

- Smoking status (never-smoker, current smoker, ex-smoker)
- BMI (underweight, normal, overweight, obese)
- Alcohol status (never-drinker, current drinker, ex-drinker)
- Index of multiple deprivation score

*Interaction*

We will fit interaction terms to explore possible effect modification between exposure to a PDE5 inhibitor and age, smoking status and index of multiple deprivation score.

*Sensitivity analysis*

As a sensitivity analysis we will exclude the first 12 months of follow up after index date in both exposed and unexposed patients. This is to decrease the chance of reverse causality, whereby undiagnosed melanoma cancers cause ED and hence the need for a PDE5 inhibitor prescription.

We will also conduct an analysis restricted to patients diagnosed with diabetes as previous restrictions mean all patients diagnosed with diabetes were definitely eligible for a PDE5 prescription.

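### In the 12-month reverse-causality analysis, melanomas in the year after a control's own first prescription count in neither group, which can leave a small upward residual in the hazard ratio

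*Combined protocol and SAP*

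**What the plan says.** Three rules meet here.

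- **Sensitivity analysis (Statistical/analysis plan).** The plan will "exclude the first 12 months of follow up after index date in both exposed and unexposed patients". The aim is modest: "This is to decrease the chance of reverse causality". The mechanism named is that "undiagnosed melanoma cancers cause ED and hence the need for a PDE5 inhibitor prescription".
- **Control censoring (Study Population).** For a control who later starts treatment, "in this situation they will be censored as a control at the time of starting a PDE5 inhibitor". He then re-enters as an exposed man, with a new index date and his own matched controls. The Statistical/analysis plan repeats the rule in its list of events that end observation: "prescription of a PDE5 inhibitor (for unexposed controls), or end of follow up".
- **Model.** Cox regression, "stratified by matched set to account for the matching".

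The sensitivity analysis paragraph gives no different censoring rule for controls. The section on changes from the protocol reports no change to this analysis.

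**The concern.** Take a man three years into follow-up as a control who has an undiagnosed melanoma, develops ED, receives a first prescription and is diagnosed four months later. He left the control group on the prescription date, so his melanoma is not a control event. It falls in the first year of his new exposed record, which this analysis drops, so it is not an exposed event either.

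The 12-month allowance is thus applied where exposed time begins but not where control time ends. Dropping the first 12 months after the control's own index date does not help, because his switch can come at any later time. Under the plan's own mechanism, the men who leave control time by switching include more than their share of those about to be diagnosed. The control rate is then too low, and the error has the same direction as the bias under test. This is the only pre-specified analysis aimed at reverse causality, so its residual bias should be known when its result is read.

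**Working it through.** **The plan's own figure.** The documents give no number for this analysis. The nearest yardstick is the detectable effect of about 1.18 in the sample size section (179,298 exposed, 1:1, 0.27% melanoma, 80% power, 5% significance). Recomputed two-sided, the detectable effect is 1.19 with 0.27% taken as the control proportion and 1.21 with it taken as the exposed proportion. A one-sided 5% test with 0.27% in the exposed gives 79.6% power at 1.18. The point below does not depend on this figure.

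**Assumed inputs (none is in the documents).** No drug effect; melanoma rate λ; controls start a PDE5 inhibitor at rate *a* per year; that rate is multiplied by *k* during the *L* years before a melanoma diagnosis (latency). Equivalently, the melanoma rate is *k* times λ for *L* years after a start.

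**Residual under the planned rule, L at most 1 year.**

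1. Exposed time after month 12 has rate λ, because the raised period has been dropped.
2. A man diagnosed as a control must not have started in the preceding *L* years. Relative to other controls, his chance of still being uncensored is multiplied by exp(−a(k−1)L). The observed control rate is therefore λ·exp(−a(k−1)L).
3. The hazard ratio is exp(a(k−1)L). With L = 1:

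| Start rate a | k = 1 | k = 2 | k = 3 |
|---|---|---|---|
| 1% a year | 1.000 | 1.010 | 1.020 |
| 2% a year | 1.000 | 1.020 | 1.041 |
| 3% a year | 1.000 | 1.030 | 1.062 |

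A cruder route agrees. The share of control time within a year after a start is a/(1+a), so the inflation is 1 + [a/(1+a)](k−1). This gives 1.010 at 1% and k = 2, and 1.058 at 3% and k = 3.

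**What the exclusion already achieves (L = 1, 6 years of follow-up assumed).**

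| a, k | Main analysis | After exclusion | Excess removed |
|---|---|---|---|
| 1.5%, 2 | 1.191 | 1.015 | 0.176/0.191 = 92% |
| 3%, 3 | 1.443 | 1.062 | 0.381/0.443 = 86% |
| 3%, 5 | 1.937 | 1.127 | 0.810/0.937 = 86% |

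**With control censoring also lagged 12 months.** Starts in the last 12 months no longer censor, so the exponent becomes a(k−1)·max(L−1, 0). This is zero for L up to 1 year, and the hazard ratio is 1.00. A simulation of 6 million men at a = 3% and k = 5 gave 1.128 under the planned exclusion and 1.005 with the lag. Its main-analysis ratio was 1.84, below the 1.94 above, because it used crude rates and a deliberately high melanoma rate of 1% a year.

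**Longer latency.** With L = 2, a = 1.5% and k = 2, the ratio is 1.384 in the main analysis, 1.243 after the exclusion and 1.224 with the lag added. Most of what remains comes from the exposed men's second year, which a 12-month window does not reach.

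**Scale.** The sample size section implies 179,298 × 0.0027 ≈ 484 exposed melanomas. Assuming the same proportion in four controls each (1,936), SE(log HR) ≈ √(1/484 + 1/1936) ≈ 0.051. Residuals of 0.01 to 0.06 on the log scale are about 0.2 to 1.2 standard errors, and less once first-year events are dropped. For the residual alone to reach 1.18, k must be 1 + ln(1.18)/a, which is about 12 at a = 1.5% and 6.5 at a = 3%.

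**The case against.** The strongest reply is that the analysis does what it says. It is described as an exclusion applied equally to both groups, and it claims only to decrease the chance of reverse causality. A reader might infer that it was meant to move early melanomas into unexposed time and fails to do so. The documents do not support that: nothing in them promises a lagged-exposure analysis or any reassignment of events. This part of the reply stands.

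Three further points also stand. The residual needs k above 1. In the middle case (1.5% a year, k = 2) it is 1.5%, well inside one standard error. And the analysis no longer stands alone: the section on changes from the protocol adds an analysis by time since first prescription and three negative control outcomes, although none of these is said to alter how controls are censored.

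The lagged alternative has weaknesses too. It places up to 12 months of on-drug time in the control group. If the drug acts early, or if the prescribing contact itself brings a diagnosis forward, those melanomas become control events and the hazard ratio can be biased downward. That is a reason to keep both versions. It does not show that the planned version is free of bias: when k exceeds 1, the direction of its residual is known and the documents neither mention nor correct it.

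**Conclusion.** The point holds as a small, conditional bias. The asymmetry follows directly from the stated rules. With no drug effect and latency of at most 12 months, it leaves the hazard ratio about 1% to 6% too high for start rates of 1% to 3% a year and a rate ratio of 2 to 3, about 13% at the extreme examined (3%, k = 5), and unbiased if the rate ratio is 1. All of these inputs are assumed.

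A reader might go further and conclude that the 12-month analysis is ineffective, or that a raised hazard ratio persisting after the exclusion could be due to this residual alone. Neither follows. In the cases shown with latency up to 12 months, the exclusion removes about 86% or more of the excess, and explaining a ratio of 1.18 would take a rate ratio of roughly 6.5 to 12 at start rates of 3% to 1.5%. If latency is longer than 12 months, the short window matters more than the censoring rule.

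**What to change.** Keep the planned exclusion and the main analysis as they are. State explicitly how controls who start a PDE5 inhibitor are censored in the 12-month analysis. Then add a lagged version beside it:

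- A control's follow-up ends 12 months after his own first PDE5 inhibitor prescription, or earlier at melanoma, another cancer, death, transfer out or end of follow-up.
- His own exposed record starts at month 12, so none of his time is counted in both roles.
- The first 12 months after index remain excluded in both groups, and the model is unchanged.

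Report the two hazard ratios together with the limits of the lagged one: it treats up to 12 months of on-drug time as unexposed, it can err downward if the drug acts early or the prescribing contact prompts diagnosis, and it removes the residual fully only if latency is at most 12 months.

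The cost is one changed censoring date for controls in one added sensitivity analysis. No new data are needed.

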**Limitations**

*Missing data*

Although there is known missingness in the smoking and alcohol status and BMI variables, this is minimal. Initial feasibility analyses using a CPRD random sample show that 2.3% and 1% of patients prescribed a PDE5 inhibitor have missing data for alcohol status and smoking status respectively. We plan to conduct a complete case analysis, which relies on the assumption that the probability of these data being missing is independent of melanoma risk, conditional on covariates [7]; given the small amount of missing data, any violation of the assumption is unlikely to importantly affect the results.

*Lack of data on UV Exposure*

UV exposure is a strong risk factor for malignant melanoma, though it is unclear as to whether UV exposure is likely to be associated with PDE5 inhibitor use and therefore a potential confounder. As data on patient level UV exposure are unavailable, we will match on GP practice as we believe patients from the same practice will have similar sun exposures whilst at home due to geographical location, though a limitation is that it will be impossible for us to take account of amount of time spent outdoors. We will also adjust for index of multiple deprivation score as we believe this will to some extent act as a proxy for amount of travel abroad.

*Sale of PDE5 inhibitors without a prescription*

There is a high volume of PDE5 inhibitors, especially sildenafil (marked as Viagra), sold illegally. It is therefore possible that patients could obtain medication without a prescription resulting in exposure status misclassification. If this is the case, it would result in an underestimation of the true effect size.

**CHANGES FROM THE PROTOCOL AND EXPLANATION**

We added an extra exclusion criteria: men with no consultation in the year prior to the index date were excluded from the study. This is because we initially discovered a large discrepancy in the proportion of non-consulting patients between the exposed and unexposed groups, with the unexposed much more likely to be non-consulters, implying a potential for substantial differences in ascertainment of outcomes, and therefore bias. All analyses were otherwise carried out as pre-specified, but we conducted some further analyses to assess causality and exclude bias, as follows:

1. We added an extra secondary analysis to investigate changes in the association between PDE5 use and melanoma by time since first prescription date. This was to further explore whether patterns of effects were consistent with causality.

2. We investigated interaction by practice region, as well as by the pre-specified potential effect modifiers. This was because of an apparent important role for sun exposure; the climate in the southern UK is generally warmer with more hours of sunshine than in the northern part of the country.

3. We added three negative control outcomes (basal cell carcinoma, solar keratosis, colorectal cancer) as a way of excluding bias. No causal effects of PDE5 inhibitor use were postulated for these outcomes. The specific outcomes were chosen to incorporate one non-melanoma skin malignancy, one non-malignant skin condition, and one condition unrelated to skin.

4. We conducted a post-hoc analysis to relate PDE5 exposure to prior solar keratosis, in order to assess possible confounding by sun exposure.

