**Exposures and outcome**

*Exposure*

- Primary exposure – Ever received a PDE5 inhibitor prescription (time-updated)

An incident PDE5 inhibitor prescription will be identified by an appropriate therapy code in the patient’s therapy records (relevant code list in appendix 1). To be considered incident, the first prescription must be at least 12 months after initial registration into CPRD as prescriptions within this period could be continuation of a prescriptions from a prior GP, of unknown duration. All matched controls must also have one year of post registration follow up prior to index date.

- Secondary exposure – Cumulative number of PDE5 inhibitor prescriptions (time-updated)

All subsequent prescriptions will be identified and the cumulative number of prescriptions will be categorised into the following groups: 1, 2-4, 5-10, 10-20 and 20+.

Number of prescriptions prescribed to patients will be used as a secondary exposure instead of cumulative duration of prescription because PDE5 inhibitors are prescribed for a patients to take as required. We are unable to judge the sexual activity of patients, hence any estimations made in an attempt to identify the length of time until a patient runs out of tablets will be unreliable. As a further analysis we will use the cumulative number of tablets prescribed to a patient as an exposure.

*Outcome*

The primary outcome is incident malignant melanoma, identified by an appropriate Read code in the patients’ medical record (relevant code list in appendix 2).

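### The added consultation rule uses a window that ends at the prescribing contact in exposed men but at a borrowed date in controls, so it is not the same test in both groups and can leave a residual bias towards a lower HR

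*Combined protocol and SAP*

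**What the plan says.** The section on changes from the protocol adds one exclusion: "men with no consultation in the year prior to the index date were excluded from the study". Its reason is a discrepancy seen in the data, "with the unexposed much more likely to be non-consulters, implying a potential for substantial differences in ascertainment of outcomes, and therefore bias". No proportions are given, before or after the exclusion. The section does not define a consultation, set a gap before the index date, discount any type of visit, or say how contacts on the index date were treated.

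The index date is defined under Study Population. For exposed men, "Follow up will begin at the date of first PDE5 inhibitor prescription". For controls, "their index date will be the same as their matched" exposed man's. Under Exposures and outcome, "An incident PDE5 inhibitor prescription will be identified by an appropriate therapy code in the patient’s therapy records", so becoming exposed requires contact with the practice. The same section guarantees 12 months of look-back: an exposed man's first prescription must come at least 12 months after registration, and "All matched controls must also have one year of post registration follow up prior to index date".

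Consulting is not a matching variable; Study Population lists age, practice and diabetes status. Nor is it in the adjustment set, which is smoking, BMI, alcohol and deprivation.

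**The concern.** The rule is worded identically for both groups but does not test the same thing. In an exposed man the window closes at an event that he reached by seeking care. Visits in which he raised erectile dysfunction (ED), or was assessed for it, can fall inside the window and satisfy the rule whatever his usual habit. A control's window closes on a date unrelated to his own care, so he must have consulted for some other reason.

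If that happens often enough, habitual low consulters stay in the exposed group while their counterparts leave the control group. If low consulters are also less likely to have a melanoma recorded, the comparison tilts towards a lower HR. The rule was brought in against the opposite tilt, better recording in the exposed. In a study asking whether a drug raises melanoma risk, a residual bias downwards is a bias towards missing harm. As an eligibility criterion, the rule reaches every analysis, including the primary HR.

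The same visits may also account for part of the discrepancy that led to the rule, if it was measured over the same window.

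**Working it through.** The documents contain no figure for the consultation rule, so there is nothing of the plan's to reproduce. What follows shows direction and plausible range; every input is an assumption.

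**Inputs (all assumed)**
- P: share of men in a group with no consultation in the window other than for ED.
- q: probability that such a man, if exposed, passes the rule on a counted ED visit. In controls q = 0.
- d: rate at which melanoma is recorded in such men relative to other men.
- No drug effect, so any ratio other than 1 is bias.

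**Formulas**
- Before the rule: ratio = [(1 − P_exp) + d·P_exp] / [(1 − P_unexp) + d·P_unexp].
- After the rule, controls contain no such men. Among retained exposed men their share is s = q·P_exp / (1 − P_exp + q·P_exp), and the ratio is 1 − (1 − d)·s.

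**Equal background consulting in both groups** (ratio before the rule is 1.00)

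| P, both groups | controls kept | q = 1, d = 0.5 | q = 0.5, d = 0.5 | q = 1, d = 0.75 |
|---|---|---|---|---|
| 10% | 90% | 0.95 | 0.974 | 0.975 |
| 20% | 80% | 0.90 | 0.944 | 0.95 |
| 30% | 70% | 0.85 | 0.912 | 0.925 |

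Worked cell, P = 20%, q = 0.5, d = 0.5: s = 0.10/0.90 = 0.111, and 1 − 0.5 × 0.111 = 0.944. With q = 1, s = 0.20 and the ratio is 0.90.

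**Exposed men truly consult more** (P_unexp = 30%, d = 0.5)

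| P_exp | before the rule | after, q = 0 | after, q = 0.5 | after, q = 1 |
|---|---|---|---|---|
| 10% | 0.95/0.85 = 1.118 | 1.00 | 0.974 | 0.950 |
| 20% | 0.90/0.85 = 1.059 | 1.00 | 0.944 | 0.900 |

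With 10% in the exposed, the rule reduces the bias at every q shown, though it may reverse the sign. With 20%, the bias after the rule at q = 0.5 is as large as before it, with opposite sign (17/18 against 18/17), and at q = 1 it is larger.

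The value 1.00 at q = 0 holds by construction: if visits leading to the prescription do not count, both groups face the same test.

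**Do other parts of the plan correct it?** The 12-month sensitivity analysis removes follow-up after the index date and leaves eligibility unchanged. The analysis by time since first prescription also starts from the same selected men. Neither alters the window.

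**The case against.** The strongest reply has four parts.

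First, the rule refers to the period before the index date. Read literally, a visit on the day itself does not count, so a man prescribed at his first visit gains nothing. No passage says how many exposed men had earlier ED visits. This stands: q is unknown, and q = 1 is an upper bound.

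Second, exposed men probably do consult more for other reasons. The Background says NHS prescribing was for a long time limited to men with ED and one of a list of diagnoses, and only diabetes is matched. Few exposed men may then have needed an ED visit to pass. This also stands, and it is why the case with unequal consulting belongs beside the equal one. The same restriction also makes contact before the prescription plausible, so it does not dispose of the point.

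Third, recording depends on contact during follow-up. Exposed men who return to the practice after starting treatment may not behave as low consulters, which moves d towards 1 and shrinks the effect.

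Fourth, three negative control outcomes were added to exclude bias, and a large difference in ascertainment should show there. They can reveal net bias but cannot isolate this source. Two of them are skin conditions, and the same section raises confounding by sun exposure, which could offset a downward ascertainment bias.

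A reader might infer that the rule creates the very bias it was meant to remove, or that the primary HR is invalid. The documents support neither. The residual bias runs the other way, its size cannot be derived from anything reported, and the rule may still leave less net bias than there was without it.

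**Conclusion.** The asymmetry is real and can be read from the text: an unlagged window ends at a prescribing contact in one group and at a copied date in the other, with no matching, adjustment or sensitivity analysis on consulting. Its direction, if low consulters are less often diagnosed, is towards a lower HR.

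Its size is unknown. With recording at half the rate in otherwise non-consulting men, and these men 20% of both groups, the null HR would be 0.94 to 0.90 as q goes from one half to one. With 30% of unexposed and 10% of exposed men, it would move from 1.12 to between 1.00 and 0.95. For scale only, the sample size section gives about 1.18 as the effect detectable with 80% power at 1:1 matching; that is not a target effect.

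This is a cheap improvement to a reasonable rule. It does not call for replacing the primary analysis.

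**What to change.** Keep the primary population and add one sensitivity analysis of the primary Cox model:

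- Require at least one consultation in a window that ends before the prescribing episode, for example 12 to 3 months before the index date, in exposed men and controls alike.
- Never count index-day contacts.
- Rebuild the matched sets under this rule and refit the model.

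Alongside it, define a consultation, state whether index-day contacts counted in the analysis already done, and report the proportion of non-consulters by group under both windows, before and after exclusion. The most informative figure is the share of men kept by the current rule who had no contact in the lagged window, compared between groups: an excess in the exposed is what this mechanism predicts. If the two HRs differ, temper the conclusion.

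The lagged window lies inside the 12 months of registration already required, so it should need no new data. The cost is a little more analysis, a short addition to the text, and somewhat more men excluded in that analysis, because the window is 9 months instead of 12. The 3-month gap is a judgement and should be stated as one.

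### Excluding men with no consultation in the prior year removes the imbalance in non-consulters, but consultation frequency among the men who remain is neither matched nor adjusted for, so some ascertainment bias could persist

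*Combined protocol and SAP*

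**What the plan says.** The section on changes from the protocol reports "a large discrepancy in the proportion of non-consulting patients between the exposed and unexposed groups" and gives the direction and consequence: "with the unexposed much more likely to be non-consulters, implying a potential for substantial differences in ascertainment of outcomes, and therefore bias". The remedy is one extra exclusion: "men with no consultation in the year prior to the index date were excluded from the study". The section then states: "All analyses were otherwise carried out as pre-specified". It lists further analyses but no added covariate.

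Under Confounding, the matching is summarised as "Age, GP practice, diabetes status and calendar time are matching variables". The covariates follow: "Our models will also be adjusted for the following potential confounders evaluated at beginning of follow up". They are smoking, BMI, alcohol and deprivation score. Consultation frequency is in neither list, and Study Population does not mention it.

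On the outcome, Exposures and outcome says: "The primary outcome is incident malignant melanoma, identified by an appropriate Read code".

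The plan also looks for residual bias: "We added three negative control outcomes (basal cell carcinoma, solar keratosis, colorectal cancer) as a way of excluding bias". It adds an analysis by time since first prescription. A sensitivity analysis drops the first 12 months of follow-up, for the stated reason of reverse causality.

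**The concern.** The plan's argument is that less GP contact means fewer recorded outcomes. Nothing in that argument stops at one visit a year. A man seen once and a man seen ten times both pass the exclusion, yet their chances of having a lesion noticed and coded may differ.

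The design gives some reason to expect users to consult more even among consulters. Exposure requires a prescription in the GP record. According to the Background, eligibility was for most of the study period tied to listed diagnoses including diabetes, renal failure and severe distress. Of these, only diabetes is matched. Visits leading up to the prescription may also count towards a user's prior year, and a control has no counterpart to them.

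If users do consult more and recording rises with contact, the melanoma hazard ratio moves upward, the same direction as the effect under test. The outcome is rare and the cohort very large, so a modest bias could pass for a modest effect.

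**Working it through.** **The plan's yardstick.** Sample size/power calculation gives 179,298 exposed men, about 0.27% with melanoma, 1:1 matching, 80% power, 5% significance and a detectable effect of about 1.18. A pooled two-proportion calculation gives:

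| Reading | N per group for 1.18 | Power at 1.18 | Detectable ratio |
|---|---|---|---|
| 0.27% in exposed, one-sided 5% | 181,348 | 79.6% | 1.181 |
| 0.27% in unexposed, two-sided 5% | 195,018 | 76.6% | 1.188 |
| 0.27% in exposed, two-sided 5% | 230,225 | 69.6% | 1.208 |

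The first row reproduces the figure. The plan does not state sidedness, and this point does not depend on it. At 1:4, two-sided, the detectable ratio is about 1.15 to 1.16. The 1.18 serves only as a scale for the bias.

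**Residual bias.** The documents give no non-consulter percentages, no consultation counts and no link between contact and recording. Every input below is an assumption, and the true hazard ratio is taken as 1.

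*(a) Only any-versus-none contact matters.* Suppose 14.3% of users and 25% of controls are non-consulters and non-consulters have no melanoma recorded.
- Before the exclusion: (1 − 0.143)/(1 − 0.25) = 0.857/0.75 = 1.14.
- After it: 1.00. The exclusion is a complete cure.

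*(b) Two levels of consulting among the men who remain.* Let a share p₁ of users and p₀ of controls be frequent consulters, with recorded rate d times that of the others. Then the spurious HR = [1 + (d − 1)p₁]/[1 + (d − 1)p₀].

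| p₁ | p₀ | d | Spurious HR after exclusion |
|---|---|---|---|
| 0.50 | 0.45 | 1.2 | 1.009 |
| 0.45 | 0.30 | 1.3 | 1.135/1.09 = 1.041 |
| 0.45 | 0.30 | 1.5 | 1.225/1.15 = 1.065 |
| 0.50 | 0.30 | 2.0 | 1.154 |
| 0.60 | 0.30 | 2.0 | 1.6/1.3 = 1.231 |

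On the log scale the two moderate rows are ln 1.041/ln 1.18 = 0.24 and ln 1.065/ln 1.18 = 0.38 of the detectable effect.

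*(c) Recording rises with each visit.* Visits follow a negative binomial distribution with dispersion parameter 1. The recorded rate is multiplied by exp(β) per visit, capped at 20 visits. Excluding zeros truncates both distributions.

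| Mean visits, users vs controls | β | HR before exclusion | HR after exclusion |
|---|---|---|---|
| 6 vs 5 | 0.02 | 1.019 | 1.018 |
| 6 vs 5 | 0.05 | 1.052 | 1.050 |
| 6 vs 4 | 0.02 | 1.039 | 1.038 |
| 6 vs 4 | 0.05 | 1.111 | 1.108 |
| 6 vs 3 | 0.02 | 1.060 | 1.059 |
| 6 vs 3 | 0.05 | 1.177 | 1.172 |

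Under a graded relation the exclusion removes almost none of the bias. Whether the exclusion suffices therefore turns on the shape of the contact–recording relation, which the documents neither state nor test.

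**The case against.** The imbalance the plan names is in the proportion of non-consulters, and the exclusion removes that by construction for the baseline year. A reader might infer that the plan concedes a remaining imbalance in frequency. It does not, and no figure in the documents shows one. This objection stands: residual bias is possible, not demonstrated.

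The plan also has safeguards. If users were simply recorded more often for everything, the colorectal cancer hazard ratio should rise too, so that outcome is a real test of general ascertainment. The analyses by time since first prescription, by cumulative prescriptions and without the first 12 months also bear on the question. All this deserves credit, but it has limits. These analyses can reveal a bias without correcting the melanoma estimate. Raised hazard ratios for basal cell carcinoma and solar keratosis could reflect sun exposure or closer skin examination, and cannot tell the two apart. A null for colorectal cancer would not exclude detection specific to skin. The post-hoc analysis of prior solar keratosis has a similar difficulty, since recording that condition also depends on contact.

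Lastly, a baseline count misses GP contact after index, such as visits for repeat prescriptions, and frequency may partly stand for comorbidity. Both are fair, and both favour an additional analysis over a replacement for the main model.

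**Conclusion.** The point holds as a gap in adjustment. The plan's own ascertainment argument extends to how often men consult, and frequency is not controlled in any described analysis. The spurious hazard ratio left after the exclusion runs from 1.00, through about 1.04 to 1.07 with moderate inputs, to about 1.23 with extreme ones. All rest on assumed consulting shares or means and assumed recording gradients. An upward direction requires both that users consult more among the men who remain and that recording rises with contact.

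Two stronger readings are not supported. One is that the bias matches the effect the study was built to detect: moderate inputs give about a quarter to two-fifths of ln 1.18, and only the extreme ones reach or exceed it. The other is that users and controls faced different consultation rules: the text states one rule for all men and does not say how visits leading to the prescription were handled.

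This is an inexpensive improvement worth making. It does not show that the reported association is biased.

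**What to change.** 1. Tabulate the number of consultations in the 12 months before index by exposure group, after the exclusion.
2. Add an analysis that puts categorised baseline consultation frequency (for example 1–2, 3–5, 6–10, more than 10) into the adjusted Cox models for melanoma and for the three negative-control outcomes. Omit the index date and a short window before it, for example 30 days, from the count in both groups. Some retained men will then have a count of zero, so include that category.
3. Report hazard ratios with and without the covariate, and label the analysis as added after the protocol.
4. State as a limitation that a baseline count does not deal with extra GP contact after index.

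The consultation records were already used for the exclusion, so the cost is one derived covariate and a few model runs. The downside is possible slight over-adjustment, which showing both estimates makes visible. If the estimate barely moves, the conclusion is stronger; if it moves, readers need to know.
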